### Study Population

Participants will be included in the study based on the following criteria: (1) self-identify as being of Black race, (2) pregnant with gestational age 20 to 28 weeks at enrollment, (3) ability to read and write in the English language, (4) planning to give birth in a health care facility and receive obstetrical care with a health care record, (5) reside within 20 minutes of the identified metropolitan area, (6) 19 to 51 years of age, and (7) own a smartphone with internet access. Participants will be excluded from the study for the following reasons: (1) current involvement in another intervention study, (2) planned pregnancy termination, or (3) inability to provide informed consent.

### Intervention

#### Overview

The PARITY program is designed to occur throughout the pregnancy continuum (first trimester through 12 months post partum). For the purposes of this study, the PARITY program will be shortened in length and scope to show feasibility for a larger trial. Participants will be enrolled in the study from 20 to 28 weeks’ gestation of pregnancy and will complete postintervention surveys at 6 to 12 weeks post partum. All participants (intervention and information control groups) will receive routine care from obstetric providers (not paid for by the study), printed materials about having a healthy pregnancy, printed materials about community resources, and printed materials with a referral to a birth doula if interested (paid for by the study as an incentive).

The PARITY program involves 2 parts. The first is a wellness technology platform that includes a wellness curriculum and reinforcing SMS motivational messages with links to in-depth wellness content. The second is Black community–based doula support, delivered both in-person and through the technology platform.

The mobile technology component of the intervention is a web-based platform hosted by GoMo Health delivered over a 12-week period and will end before birth [28]. The platform includes web pages with various pregnancy-related wellness content. The content is evidence based, tested by GoMo Health, and based on our preliminary research [21,28]. Participants will receive SMS *text* messages from the web platform, and at times these will include hyperlinks. The doula will be able to communicate with participants, reinforce its content, and hold the intervention sessions within this platform [28]. The platform was approved by the University of Nebraska Medical Center Information Technology Services and is compliant with the Health Insurance Portability and Accountability Act. Participants in the intervention group will receive 4 sessions with the doula interventionist within the technology platform and 12 weeks of tailored wellness, strengths, and health care adherence curriculum and SMS text messaging through the platform. There is a comprehensive database to track calls, opened hyperlinks, and participant engagement with the platform.

#### Components of the Intervention

##### Strengths

Participants will receive 12 strengths-focused SMS text messages sent through the web-based technology platform. They will also receive 4 wellness messages with hyperlinks to more in-depth educational content within the web platform related to nutrition, physical activity, and sleep. The content of the messages for this study will be tailored to maternal wellness in Black women and informed by focus groups comprising Black community members [29]. In total, participants will receive 24 SMS text messages over 12 weeks. Messages will focus on improving self-perception, reminding women they can make positive changes and be healthy, instilling a sense of optimism for the future, and imparting competence regarding challenges that may be faced throughout pregnancy and beyond. In addition, messages will convey how strengths can provide buffers against adversity and promote resilience to risk. Messages that promote positive feelings, such as gratitude, humor, and hope, will also be reinforced through a strengths-focused framework.

##### Nutrition

PARITY includes information on nutrition during pregnancy and beyond. Nutritional advice will focus on eating foods in unprocessed forms (eg, fruits, vegetables, and lean meat), preparing food instead of purchasing fast food, mindfulness in eating, and water consumption. These nutritional guidelines are consistent with healthy weight gain and multiple nutritional benefits without prescribing standards that may require excessive financial resources or exclude foods that may be culturally important to participants.

##### Physical Activity

PARITY includes approaches to increase physical activity and reduce sedentary behaviors. The goal is to significantly increase each individual’s physical activity level above baseline. Emphasis will be placed on approaches to exercise safely in pregnancy, finding joy in body movement, walking, and easy ways to reduce sedentary behavior in daily life (eg, using the stairs instead of the elevator).

##### Sleep

The sleep component of the PARITY intervention addresses ways to improve the quality and duration of sleep in pregnancy and beyond. The content will focus on the benefits of sleep to wellness and pregnancy, sleep hygiene, and troubleshooting sleep problems. Strategies, such as relaxation techniques, regularizing the sleep schedule, stimulus control, and adjusting the bedtime will be included. Specific strategies for improving sleep duration and quality during pregnancy related to nighttime waking and nocturia will also be discussed.

#### Health Care Adherence

Health care adherence content will include general reminders about adhering to the patient’s individually prescribed health care plan and reminders of appointments. The content will also include information on how to approach health care providers with questions and concerns and the importance of engaging with the medical system despite current or past negative experiences and resources on accessing care if needed.

#### Doula Sessions

Each participant will work with a Black community–based doula interventionist who will communicate with them via the PARITY mobile technology platform during the study. The doula interventionist will have certifications as a doula and training in emotional and educational support, pregnancy health, privacy and confidentiality, inspiring change (theories of health), various learning styles, health literacy, and cultural competency. All doula sessions will be conducted by the same doula interventionist, who will be blinded to all outcome data.

The SMS text messaging will be sent in the doula’s voice. The doula interventionist will communicate with each participant in 4 live sessions lasting 30 to 60 minutes. These live conversations will include basic instruction and open-ended conversations focused on reinforcing strengths and wellness habits. In addition, these check-ins will promote health care adherence and provide guidance on navigating the health care system. The doula interventionists will assist participants through the strengths-focused framework of maternal adaptive capacity to identify and understand each participant’s particular barriers to wellness and health care adherence and to design approaches that increase behavioral change [24]. The doula interventionist will suggest community resources based on the participant’s needs.

#### Qualitative Interviews

The qualitative interview uses the strengths-focused framework of the theory of maternal adaptive capacity to better understand the acceptability of the intervention and its role in emphasizing protective assets in Black pregnant women [24]. A total of 10 to 15 participants from the intervention group will be interviewed at 12 weeks post partum. A semistructured interview guide will be used to gather in-depth qualitative information. The interview guide consists of open-ended questions and additional probes that explore participants’ experiences and opinions regarding the various intervention components. The interviewer will have the flexibility to ask additional questions for further clarification and to ensure comprehensive understanding.

### Information Control Group

Participants assigned to the information control group will receive routine care from obstetric providers (not paid for by study), printed materials about having a healthy pregnancy, printed materials about community resources, and printed materials with a referral to a birth doula if interested (paid for by the study and offered as an incentive).

### Outcomes

The feasibility of a full trial will be monitored throughout the study (eg, the randomization, recruitment, and retention of participants; data collection; and adherence). Additional data will be collected only on intervention participants. These include data on engagement with the PARITY intervention based on the number of hyperlinks clicked, time engaged in the content, and the number of doula sessions completed throughout the 12 weeks. A total of 10 to 15 intervention participants will be asked to complete a qualitative interview to discuss their experiences with the intervention and the acceptability of the technology component, doula component, and strength messaging component at 12 weeks post partum.

Clinical maternal outcomes (maternal blood pressure, gestational weight gain, delivery modality, and exploratory perinatal outcomes) will be measured at 20 weeks, 36 weeks, birth, and 6 weeks post partum and will be collected from the medical record. At baseline (20-28 weeks’ gestation), demographics, discrimination, and neighborhood variables will be assessed using self-report questionnaires administered via REDCap (Research Electronic Data Capture; version 14.3.11) [30,31]. At baseline and 6 to 12 weeks post partum, wellness-related behavior outcomes (nutritional intake, physical activity, and sleep quality) and empowered strengths (self-efficacy, social support, problem-solving, motivation, resilience, and self-regulation) will be measured using web-based self-report questionnaires in REDCap. In addition, health care adherence (the number of prenatal appointments) will be evaluated retrospectively using medical records.

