Maternal blood pressure (primary) at 20 weeks, 36 weeks, birth, and 6 weeks post partum will be measured retrospectively from the medical record at 12 weeks post partum. The data will be analyzed as a continuous variable using the participant’s blood pressure (systolic and diastolic) as well as categorically with the blood pressure classifications of hypertension (>140/90) and severe hypertension (>160/110).Gestational weight gain (secondary), or the amount of weight gained in pounds at 20 weeks, birth, and 6 weeks post partum, will be measured retrospectively from the medical record at 12 weeks post partum.Cesarean birth (secondary) will be assessed from the delivery modality (vaginal, cesarean, or assisted vaginal delivery), measured retrospectively from the medical record at 12 weeks post partum.Perinatal outcomes (exploratory) from birth will be measured retrospectively at 12 weeks post partum via the maternal medical record. The perinatal outcomes that will be measured include preterm delivery; gestational diabetes; birth weight; gestational age at delivery; anesthesia used during labor; labor length; delivery provider type (obstetric physician, family physician, resident physician, or certified nurse midwife); and intrapartum medical diagnoses according to theInternational Classification of Diseases, 10th Revision[34], including hypertensive disorders of pregnancy, intrapartum fever, and postpartum hemorrhage. In addition, the Appearance, Pulse, Grimace response, Activity, and Respiration score of the newborn at birth will be measured as a way to summarize the health of the baby [35].

The following outcome measures will be used to investigate changes to wellness behavioral outcomes and empowered strengths:

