Wellness-related behavioral outcomes:*Nutritional intake* will be measured with the Multifactor Screener, 2000, as used in the Observing Protein and Energy Nutrition Study [36]. This instrument measures approximate intakes of fruits and vegetables and percentage energy from fat and fiber. Respondents will report through a self-administered questionnaire in REDCap how frequently they consume foods in 16 categories and the type of milk consumed. The questionnaire will measure nutrition at baseline and 6 to 12 weeks post partum.*Physical activity* will be measured with the International Physical Activity Questionnaire-Short Form (IPAQ-SF) [37]. The IPAQ-SF consists of 9 items and collects information on the time spent walking, in vigorous and moderate intensity activity, and in sedentary activity over the last 7 days. It is scored by converting the reported time into metabolic equivalent of task (MET) minutes. The MET minutes are then summed to provide an understanding of an individual’s physical activity levels, with low levels being <600 MET minutes per week, moderate activity levels being 600 to 2999 MET minutes per week, and high activity levels being ≥3000 MET minutes per week [37]. It will be self-administered in REDCap and takes approximately 10 minutes to complete. The IPAQ-SF is a reliable (α>.80) and valid instrument [37]. Physical activity will be measured at baseline and 6 to 12 weeks post partum.*Sleep quality* will be measured using the Pittsburgh Sleep Quality Index, a reliable (α>.83) and valid self-report questionnaire that assesses sleep quality over a 1-month time interval [38]. The measure consists of 19 individual items, creating 7 component scores that range from 0 to 3 points. The 7 component scores are summed to produce 1 global score that ranges from 0 to 21 points, with 0 indicating no difficulty and 21 indicating severe difficulty across all areas [38]. Sleep quality will be measured through a self-administered survey, which takes about 15 minutes to complete, in REDCap at baseline and 6 to 12 weeks post partum.*Health care adherence* will be measured by the number of health care appointments attended and missed, which will be logged in the medical record. Health care adherence will be measured throughout the pregnancy continuum and collected at 12 weeks post partum retrospectively via the medical record.Empowered strengths:*Self-efficacy* will be measured using the General Self-Efficacy scale [39] administered in REDCap. The General Self-Efficacy scale is a valid and reliable (α>.75-.90) 1D self-report measure that features a 10-item questionnaire assessing the optimistic self-beliefs of individuals to cope with various challenging demands in life [39]. It takes approximately 5 minutes to complete. The response options are presented along a Likert scale for each item, ranging from 1 (not at all true) to 4 (exactly true). The total score is calculated as the sum of the items, with a higher total score indicating more self-efficacy [39]. Self-efficacy will be measured at baseline and 6 to 12 weeks post partum.*Social support* will be measured using the 10-item Social Provisions Scale [40]. The 10-item Social Provisions Scale is a validated and reliable (α>.80) measure that assesses 5 social provisions: attachment, guidance, social integration, reliable alliance, and reassurance of worth [40]. Each item is rated on a 4-point Likert scale, ranging from 1 (strongly disagree) to 4 (strongly agree), and the individual item scores are then summed to provide a summary score ranging from 10 to 40 [40]. Higher scores indicate higher levels of social support [41]. Social Support will be measured through a self-administered survey, which takes approximately 5 to 10 minutes to complete, in REDCap at baseline and 6 to 12 weeks post partum.*Motivation* will be measured with the Self-Motivation Inventory (SMI) [42]. The SMI is a 40-item, 5-point Likert scale questionnaire that will be self-administered in REDCap and takes about 15 minutes to complete. The SMI is a valid and reliable (α>.91) instrument measuring self-motivation conceptualized as perseverance independent of external support [42]. Motivation will be measured at baseline and 6 to 12 weeks post partum.*Resilience* will be measured using the 10-item Connor-Davidson Resilience Scale [43]. The 10-item Connor-Davidson Resilience Scale is a valid and reliable (α>.85) unidimensional self-reported scale measuring resilience [43]. Respondents will self-report through a survey in REDCap by rating items on a 5-point Likert scale ranging from 0 (not true at all) to 4 (nearly all of the time). Scores range from 0 to 40, with higher scores representing higher resilience [43]. Resilience will be measured at baseline and 6 to 12 weeks post partum through the survey, which takes about 5 minutes to complete.*Problem-solving* will be measured with the Problem-Solving Inventory (PSI) [44]. The PSI is a valid and reliable (α>.86) self-report instrument that measures how well individuals make decisions and their problem-solving abilities [44]. The PSI includes 32 items using a 6-point Likert scale and takes about 10 minutes to complete. The total score of the questionnaire is the sum of all responses, with lower scores representing lower problem-solving abilities [44]. Problem-solving will be measured through a self-administered survey in REDCap at baseline and 6 to 12 weeks post partum.*Self-regulation* will be measured with the Index of Self-Regulation (ISR) [45]. The ISR is a valid and reliable (α>.87) instrument that measures the level of self-regulation for health behavior change in a 9-item scale [45]. Respondents rate items on a 5-point Likert scale, ranging from 1 (strongly disagree) to 6 (strongly agree), with higher sum scores indicating higher levels of self-regulation for a behavior [46]. Self-regulation will be measured at baseline and 6 to 23 weeks post partum in REDCap through the ISR, which takes about 5 to 10 minutes to complete [46].Other variables that will be assessed are demographics, discrimination, and neighborhood:*Demographics:* an investigator-developed form will measure demographic variables, including income, education, ethnicity, insurance, health provider, relationship status, and pregnancy history, at baseline.*Discrimination:* discrimination will be measured using the Everyday Discrimination Scale [47] through a self-administered survey in REDCap. The Everyday Discrimination Scale is a valid and reliable (α>.74) instrument that measures the frequency of chronic and routine unfair treatment in everyday life [47]. Respondents are asked to report how often they experience unfair treatment in their day-to-day life on a 6-point Likert scale ranging from 1 (never) to 6 (almost every day), with total scores ranging from 10 to 60. Higher scores indicate experiencing discrimination frequently and in a variety of situations [47]. Discrimination will be measured at baseline.*Neighborhood:* neighborhood variables will be assessed using the Neighborhood Collective Efficacy-Community Cohesion and Informal Social Control protocol from the Project on Human Development in Chicago Neighborhoods [48]. This valid and reliable (α=.82) measure includes 10 Likert-style questions that assess trust and expectations among neighbors and is used to determine how the neighborhood environment modifies risky behaviors [48]. It will be self-administered as a survey in REDCap and takes about 10 minutes to complete. The measures consist of 2 subscales, Community Cohesion and Informal Social Control, that include 5 Likert-style items, each ranging from 1 (strongly disagree) to 5 (strongly agree). Higher scores indicate greater neighborhood collective efficacy [48]. Neighborhood variables will be measured at baseline.

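### Health care adherence has two differing definitions, and neither is limited to care after randomisation or scaled to the visits that were scheduled

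*Protocol article*

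**What the plan says.** The protocol article defines the outcome in two places.

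- Outcomes section: "health care adherence (the number of prenatal appointments) will be evaluated retrospectively using medical records".
- Outcome Measures section: adherence "will be measured by the number of health care appointments attended and missed, which will be logged in the medical record". The window follows: "Health care adherence will be measured throughout the pregnancy continuum and collected at 12 weeks post partum retrospectively via the medical record".

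The Overview of the intervention uses the same term for the full-length programme, which is to run "throughout the pregnancy continuum (first trimester through 12 months post partum". Eligibility requires participants to be "pregnant with gestational age 20 to 28 weeks at enrollment". Under Participant Allocation, they are randomised once the enrolment surveys are complete, so randomisation also falls at about 20 to 28 weeks.

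The Data Analysis section applies one shared random component mixed model to all outcome families. The covariates fixed in advance are baseline nutrition, physical activity and sleep. Other baseline characteristics may be added if they differ between groups. No distribution, offset or denominator is given for adherence.

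**The concern.** The two definitions differ in three ways: type of visit (prenatal or any health care), quantity (one number, or kept and missed separately) and window (prenatal, or a continuum that elsewhere extends past birth). Two analysts could build different variables from the same charts.

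Both also share a weakness. PARITY's adherence content is about following each woman's own care plan and keeping her appointments, which is attendance relative to what was booked. A count of visits depends on three further things:

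- **Care before randomisation**, which PARITY cannot affect.
- **Length of gestation**, because a later birth allows more visits.
- **Visit frequency**, if women at higher risk are seen more often (an assumption).

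The first mainly costs precision. The other two can also be affected by treatment. The Objectives section predicts better blood pressure, and preterm delivery and gestational age at birth are exploratory outcomes. If PARITY lowered the rate of hypertension, visits could fall. If it lengthened gestation, visits would rise. Neither would be a change in adherence. The Objectives section expects appointment adherence to improve, so this outcome will be read as evidence for or against the programme.

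**Working it through.** **1. The plan's own figures.** None is given for adherence. The detectable differences in the sample size section (0.81 SD with 25 per group, 0.91 SD with 20) concern blood pressure and weight. Both reproduce at 80.1% power by the noncentral t distribution, but they do not bear on this outcome.

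**2. Assumed schedule.** The article gives none. For illustration only: a visit every 4 weeks to week 28, every 2 weeks to week 36, then weekly to birth. Care starts at week 8 to 16 and birth is at week 35 to 41. Randomisation at week 20 to 28 is from the article.

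**3. Share of visits before randomisation** = visits from start of care to randomisation / visits from start of care to birth.

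- Central case (start 12, birth 39): total = 16/4 + 8/2 + 3 = 11. Randomised at 20: (8/4)/11 = 2/11 = 18%. Randomised at 28: (16/4)/11 = 4/11 = 36%.
- Lowest (start 16, randomised 20, birth 41): 1/(3 + 4 + 5) = 1/12 = 8%.
- Highest (start 8, randomised 28, birth 35): 5/(5 + 3.5) = 5/8.5 = 59%.

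**4. Dilution of a proportion.** If attendance before randomisation is equal in the two groups, a rise of D afterwards appears in the whole-pregnancy proportion as (1 − share) × D. For D = 15 points this is 9/11 × 15 = 12.3 points or 7/11 × 15 = 9.5 points in the central case.

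**5. Noise in a count.** Earlier visits leave the difference in mean counts unchanged but add variance. Take start 12, randomisation 24 and birth 39, so 3 visits before and 8 after. Attendance rising from 70% to 85% adds 0.15 × 8 = 1.2 visits. With full attendance and care from week 12, total visits are 4 + 3.5 = 7.5 for birth at 35 weeks and 4 + 4 + 5 = 13 for birth at 41.

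**6. Shift without a change in adherence.** After week 36 the assumed schedule has one visit a week. At 70% attendance, each extra week of gestation adds 0.7 attended visits, so two weeks (1.4 visits) exceed the 1.2 in step 5. The expected proportion attended does not change.

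**7. Simulation.** 1,500 trials, 25 per group, Welch t test. Start of care uniform on 8 to 16 weeks, randomisation uniform on 20 to 28, birth normal with mean 38.7 and SD 2 (limited to 30 to 41.5), 20% of women with 1.5 times the visits, and attendance varying between women with SD 0.6 on the logit scale. Before randomisation both groups attend at the control rate. Window to birth only. Share of trials with p < .05:

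| Attendance after randomisation, control → PARITY | Count, whole pregnancy | Count, after randomisation | Proportion, whole pregnancy | Proportion, after randomisation |
|---|---|---|---|---|
| 70% → 70% | 5.3% | 6.2% | 5.5% | 5.3% |
| 70% → 85% | 28.9% | 39.7% | 58.0% | 81.2% |
| 75% → 90% | 32.9% | 44.1% | 70.7% | 90.2% |
| 80% → 90% | 16.9% | 21.7% | 44.4% | 66.5% |

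Simulation error is at most √(0.25/1500) = 1.3 percentage points. Birth timing and visit frequency were given the same distribution in both groups, so the first row does not test the mechanism in step 6.

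**The case against.** The strongest reply has four parts.

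- **Scale.** The article never says that adherence will be analysed as a raw count. Distribution and link can properly sit in an analysis plan that is not shown. This stands, and the point does not rest on that silence. It rests on two stated definitions that differ and on a stated window that begins before randomisation.
- **Denominator.** Recording missed visits already supplies it: with perfect attendance, attended / (attended + missed) is 1 whenever birth occurs. This also stands, and it makes the fix cheap. But the article does not commit to the proportion, and the Outcomes section names only a number of appointments.
- **Window.** The continuum may describe chart abstraction, not the comparison period. That is possible, but no other period is given.
- **What a proportion misses.** A woman who stops booking has no missed visits and scores perfectly, although PARITY also aims at engagement with care. This is right, and it is why counts should be kept alongside.

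A reader might infer that the outcome measures gestation and risk instead of adherence, so that the sign of any difference is unreadable. The article does not support that. Visits after randomisation are included, and randomisation balances earlier care and baseline risk in expectation. The simulation shows no material excess of false positives when birth timing is alike in both groups.

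A reader might also extend the point to gestational weight gain, recorded as "or the amount of weight gained in pounds at 20 weeks, birth, and 6 weeks post partum". Total gain is a legitimate outcome, and the time points can be read separately in a model with time effects. Calling the post-partum weight gestational gain is loose labelling, and scaling by week is a preference.

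**Conclusion.** The point holds as an inconsistency of definition together with an avoidable loss of sensitivity. The two sections must be reconciled, and neither version isolates attendance that PARITY could change. In the central case 18% to 36% of visits precede randomisation (8% to 59% over the range examined). In the main scenario power is 29% for the whole-pregnancy count and 81% for the post-randomisation proportion. The denominator alone raises it to 58% and the window alone to 40%. All these figures depend on the assumed schedule, attendance rates and spread, so the ordering is more secure than the values.

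Bias is conditional: a count shifts without a change in adherence only if PARITY alters gestation or the frequency of visits. Gestational age, preterm delivery and hypertensive disorders are recorded, so this could be examined. Adherence is one of several outcomes under the third objective of a 60-person pilot and is not the primary outcome, so the consequence is moderate. The change should still be made.

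**What to change.** State one definition in both sections:

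- **Outcome:** attended / (attended + missed) scheduled prenatal appointments from randomisation to birth.
- **Model:** binomial, with a participant-level random effect or another allowance for overdispersion, and attendance before randomisation as a covariate. Splitting the record at randomisation supplies the baseline that a single whole-pregnancy total lacks.
- **Alongside:** the number of prenatal appointments attended after randomisation, by group, read together with gestational age at birth, because the proportion does not show women who stop booking.
- **Rules to fix before the data are compared:** how rescheduled and clinic-cancelled visits are classed, and that post-partum visits, if wanted, are reported separately.

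No new contact with participants is needed. Kept and missed appointments are already to be taken from the medical record. The abstraction form must also capture the date and type of each appointment, and the wording of the protocol and analysis plan must change.
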